### Ethical considerations

#### Process of consent/Assent

The research assistants will be responsible for obtaining and ensuring informed consent by study participants. In each study phase, the research assistant will fully explain the study to potential participants and answer all questions regarding what participants will be asked to do as part of the study. Research assistants will receive training on informed consent so that during any community-based outreach activities, they can tell potential participants what to expect. In most cases the research assistant will perform the informed consent procedures as a contiguous process with recruitment. We will ensure that all participants know that their participation is completely voluntary and that they can withdraw at any time, without repercussion. Once a participant verbally indicates to the research assistant that all their questions have been satisfactorily answered, we will document that she or he has given informed consent to participate by having the participant sign an informed consent form. For HCF staff, we will only document informed consent for data collection. Consent for the HP+ intervention will be obtained at the HCF-facility level (not the staff-level). HCF staff may participate if, and only if, they want to participate in the intervention. All participants will be reminded that neither participating nor declining to participate has any impact on their employment status (HCF staff) or service provision (MSM).

We will document that she or he has given written informed consent to participate by having the participant sign an informed consent form (paper). As stated above, For HCF staff, we will only document informed consent for data collection. We understand that the informed consent does not end when it is documented but continues throughout the entire time that the participant is engaged with the study. In service of this critical point, the research assistants are responsible to ensure that the participant understands what she or he is being asked to do as part of the study throughout the time that the individual is enrolled so that is participation remains informed and volitional at all times. This will be assessed by changes in cognitive functioning or decisional impairment and assessed as needed by study staff.

We will use electronic forms to document written informed consent for MSM. This is an important security measure that avoids having a participant’s name affixed to a paper document that describes the study. Same-gender sexual behavior is still largely stigmatized in Ghana and the inadvertent disclosure of this may lead to social harms. The use of electronic documentation (e.g., signing the name into a computer tablet based touch-screen) is logistically less complex by reducing the handling of paper and it minimizes the risk of privacy breach by storing the information on a secure password-protected cloud platform—not on the computer tablet device itself.

#### Confidentiality and security of data

We will only collect the minimum contact information necessary to be able to reach participants for scheduling and reminders about the study visits, HP+ intervention, 3MV/Nyansapo intervention, and HIVE^3^ peer support sessions and data collection. We will collect a participant’s first name (or alias), cell phone number, and e-mail addresses. We will not collect information such as home address as to avoid the risk that unauthorized persons can apprehend and use it to identify study participants. We will also ask participants to provide an emergency number of a trusted family member or friend that we can call in the event of a medical or legal emergency. For HCF staff, we will also record the HCF site where they are employed. No research materials will contain the participant’s name. Instead, Participant ID numbers will represent a participant’s identity and will be the only link to identifying information. This key, linking participant IDs and contact information, will be stored alone on an encrypted server. At study completion, the key will be destroyed.

Three sites will be responsible for data collection and intervention delivery. The Ghanaian research NGO will provide data collection and data management services for the overall study. This will include establishing and training a team of research assistants who will obtain informed consent and conduct data collection in the formative and randomized controlled trials phases. They will also oversee data collection and intervention implementation in the health facilities. We will recommend that participants complete the informed consent and survey procedures inside of the eight participating HCF sites. Participants will be given a paper version of the survey by study staff; study staff will then collect the surveys and enter the data into an electronic database. Data entry will be verified and the paper surveys will be destroyed. HCF staff surveys will be anonymous; HCF respondents will not be asked to provide their name, specific age, or other identifying information on the survey.

The two MSM-led organizations will provide recruitment, data collection and retention services for MSM in the study. Research assistants will recruit, obtain informed consent, collect data, and follow-up with participants to support study retention. The research assistant will record all client contact information in an online data management information system via computer tablets. We will recommend that participants complete the informed consent and survey procedures inside of our partner’s data collection sites. Survey procedures will include coming to a data collection site and completing the survey using a tablet. No paper data will be collected and data will be automatically stored in the online data collection system. If a participant prefers, a study staff member can read the questions to the participant and document the participant’s answers.

Permission to collect HIV testing data will be requested in the informed consent form. We will also ask for participants to complete an authorization for medical records release. For those who report a post- intervention HIV test, we will seek to get confirmation from the HCF that test was conducted and the test result. For participants who report HIV testing at their assigned HCF, the study nurse will verify study participants’ name against the HCFs HIV test log to confirm the test was done at the facility. The study nurse will use an internet enabled computer tablet device to record the date of the test and test result directly into the online data management system used in the study.

We will destroy all identifiers after the data analyses have been completed. We define completed as the publication of the results of the primary research questions in a scientific peer-reviewed journal. Before that time, there may arise a need to audit the data to a level that is identifiable. We will maintain the capacity to conduct such a detailed audit until the primary results are published. To maximize participant confidentiality, all data will be identified only by the subject ID number, and no participant names will appear on any research materials. All research data will be maintained on a secure computer system with actively maintained high level of security to ensure the confidentiality of our databases. Access to the list containing participant IDs will only be provided on a need-to-know basis to approved study staff.

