**Methods:**

We proposed a mixed method study among MSM in Ghana. First, we will develop the intervention protocol using the Convergence Framework, which combines three interventions that were previously implemented separately in Ghana for reducing stigma at the HCF-level, increasing HIV testing at the peer group-level, and increasing peer social support at the individual-level. Then, we will conduct a cluster randomized controlled trial with four pairs of HCFs matched on staff size. HCFs within each pair are randomized to the HCF-level stigma-reduction intervention or control arm. MSM (n = 216) will be randomized to receive the group-level and individual-level interventions or standard of care control arm. MSM will be assigned to receive HIV testing at one of the HCFs that match their study assignment (intervention or control facility). The frequency of HIV testing between MSM in the study arms at 3 and 6 months will be compared, and the predictors of HIV testing uptake at the HCF, peer group and individual-levels will be assessed using multi-level regression models.

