#### Outcomes

For MSM, we will assess important baseline characteristics for describing the sample, including: age, income, gender, education, ethnicity, relationship status, religion, sexual identity, sexual practices, HIV knowledge, HIV testing readiness, HIV testing history and histories of experiencing intersecting stigmas, access and utilization of health and social services, civic engagement and neighborhood. For HCF staff, we will assess a more limited set of baseline characteristics. Our primary outcome will be an uptake of HIV testing within six months of randomization. We will also record the frequency of HIV testing within six months, but we anticipate that few participants will take more than 1 test in this short period. Our secondary outcome will be a reduction in intersectional stigma, both at the HCF-level and among MSM participants. For HCFs, we will construct a latent variable of intersectional stigma using items from questionnaires that measure HIV stigma and discrimination and LGBT stigma among health facility staff. For intersectional stigma among MSM, we will also create a latent variable that is drawn from three scales that measure HIV stigma, same-sex stigma, and gender non-conforming stigma. Outcomes will be assessed within 3-and 6-months post-intervention for HCFs and 3- and 6-months post-intervention for MSM.

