#### Step 8 (Test)

We will conduct an RCT of the multi-level intervention with a 6-month wait-list control. In each city, we will create two pairs from the 4 HCF sites matched by the number of HIV tests performed in the calendar year 2020. We will randomly assign clinics (enveloped odd/even) within each pair to either receive the HP+ or the wait-list control. MSM will be randomly assigned to receive either Nyansapo and HIVE^3^ or wait-list control. MSM in the intervention group will be asked to follow-up for HIV testing and services at one of the HCFs assigned to the HP+ intervention and the MSM in the wait-list control group will be asked to follow-up at any of the HCFs in wait-list control. Nurses from the intervention HCFs will participate as guest facilitators in one of the Nyansapo sessions and will use that opportunity to reach out to MSM to visit their facility for testing. Our primary hypothesis is that the multi-level intervention will increase uptake of HIV testing among MSM participants. We will use research data collectors to measure frequency of HIV testing among MSM at 3- and 6-months post-intervention using a combination of self-report survey and verification by study nurses (for men who get tested for HIV at participating HCFs.) Our secondary hypothesis is that the multi-level intervention will reduce intersectional stigma that HCF staff convey and that MSM experience in HCFs. We will use research data collectors to administer a survey measuring intersectional stigma 1) in the HCFs at baseline, 3-months post and 6-months post intervention and 2) among MSM at baseline, 3- and 6-months post intervention.

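### The log check of HIV tests starts only from a self-report and has no consistent scope, and no single HCF is fixed for control men, so the HCF cluster is undefined for those who do not test

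*Protocol article*

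**What the plan says.** **Outcome.** The Outcomes section states: "Our primary outcome will be an uptake of HIV testing within six months of randomization". Step 8 (Test) says testing is measured "using a combination of self-report survey and verification by study nurses (for men who get tested for HIV at participating HCFs".

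**Scope of the check.** Confidentiality and security of data has two consecutive statements. One covers every man who reports a test: "For those who report a post- intervention HIV test, we will seek to get confirmation from the HCF that test was conducted". The next gives the working procedure, a comparison of the participant's name with the HCF's test log: "For participants who report HIV testing at their assigned HCF, the study nurse will verify".

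**Which HCF.** The abstract treats both arms alike: "MSM will be assigned to receive HIV testing at one of the HCFs that match their study assignment". Step 8 separates them. For intervention men: "MSM in the intervention group will be asked to follow-up for HIV testing and services at one of the HCFs assigned to the HP+ intervention". For control men: "the MSM in the wait-list control group will be asked to follow-up at any of the HCFs in wait-list control".

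**Identity.** The contact data to be collected are "first name (or alias), cell phone number, and e-mail addresses".

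**Model.** The Statistical analysis plan section tests the primary hypothesis with an uncorrected chi-square. It adds a logistic mixed model with HCF-level factors, because outcomes of men at the same HCF may be correlated. It also foresees some control men attending intervention HCFs.

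**The concern.** Three things are left unsettled for a binary primary outcome.

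1. **Who is checked.** A check that begins with a reported test can remove false positives. It cannot recover tests that a man forgets, conceals, or never has the chance to report because he misses the survey.
2. **Where the check looks.** If the assigned HCF sets the boundary, the rule is unclear for a control man free to use any control HCF, and for a man who crosses to the other arm's facilities.
3. **Which cluster he belongs to.** A man with no HCF fixed at randomisation acquires one only by attending. Those who attend for a test are, by definition, those with the outcome.

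The match key adds a practical weakness: a name search in a log may fail if the study knows the man by an alias.

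At stake are the completeness of the primary outcome and the validity of the clustered analysis. The trial promotes testing through group sessions and peer mentors, so pressure to report a test may also be unequal between arms.

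**Working it through.** The plan states no verification or capture rate, so there is no figure to reproduce. The main check is textual.

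**Step 1: scope of the check**

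| Place | Who is checked | Starts from self-report? |
|---|---|---|
| Step 8 (Test) | men tested at participating HCFs | not stated |
| Confidentiality and security of data, general sentence | all who report a test after the intervention | yes |
| Confidentiality and security of data, log procedure | those reporting a test at the assigned HCF | yes |

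The three scopes differ. None says that logs are searched for a man who reports no test or does not attend.

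**Step 2: how many are outside the survey.** Sample size gives 216 recruited and 172 needed at six months under 80% retention. 216 − 172 = 44 men. Their tests may stand in the logs, yet no check is described for them. The 44 come from planned attrition, not from the verification rule; the rule only fails to make use of the logs.

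**Step 3: is there an assigned HCF?** Each city has four HCFs in two pairs, one of each pair per arm: two HCFs per arm per city, four per arm overall. Under the abstract a control man has one of these. Under Step 8 he may use any of the four. The intervention wording can be read as an assignment or as a choice. The two sections cannot both govern control men.

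**Step 4: consequence for the mixed model.** The model needs an HCF for every man.
- Control man who tests: the HCF attended can be recorded.
- Control man who does not test: Step 8 gives him none.

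If the HCF attended were used, every control man with an HCF identified through testing would have outcome = yes. The cluster would then be a consequence of the outcome. The primary chi-square uses no cluster and is not affected by this step.

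**Step 5: match key.** The nurse searches by name. The listed contact data allow an alias. Other sections refer to a signed electronic consent and to the research assistant's access to name and phone number, but none says which identifier the nurse receives.

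**Step 6: would unequal capture matter?** Illustration only; the capture rates are assumptions. Observed rate = true rate × capture. Test: two-sided two-proportion z-test at 5%, 86 per arm, clustering ignored, no true effect.

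| True rate, both arms | Capture, intervention / control | Observed rates | Rejection rate |
|---|---|---|---|
| 40% | 90% / 90% | 36% / 36% | 5.0% |
| 40% | 95% / 85% | 38% / 34% | 8.5% |
| 40% | 95% / 75% | 38% / 30% | 19.7% |
| 70% | 95% / 85% | 66.5% / 59.5% | 15.8% |
| 70% | 95% / 75% | 66.5% / 52.5% | 46.4% |

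For the second row: difference 0.04; null SE = √(2 × 0.36 × 0.64 / 86) = 0.0732; SE under the observed rates = √((0.38 × 0.62 + 0.34 × 0.66) / 86) = 0.0731. Rejection = Φ((0.04 − 1.96 × 0.0732)/0.0731) + Φ((−0.04 − 1.96 × 0.0732)/0.0731) ≈ 0.079 + 0.006 = 0.085.

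Equal capture leaves the error rate at 5%; unequal capture does not.

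**The case against.** A reader might infer three stronger points. The case against each is good.

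- **That tests are verified only at the assigned HCF.** The sentence just before the log procedure promises to seek confirmation for all who report a test, and Step 8 extends nurse verification to participating HCFs. The scope is inconsistent rather than confined to one facility.
- **That the study holds nothing but a first name or alias.** That list is contact information for scheduling and reminders. The consent section describes signing a name on a tablet, a medical-records release is requested, and Data storage and access mentions name and phone number. The match key may be weak; it is not shown to be absent, and the weakness applies to both arms.
- **That ascertainment differs by arm.** Both Step 8 phrases leave more than one facility open, the abstract treats the arms alike, and self-report is collected in both. Intervention-HCF nurses do invite men at the group sessions, with no control counterpart described. But that is part of the intervention and meant to raise true testing; nothing says it makes tests easier to find in a log. False reporting by 10–20% of intervention non-testers would lift 40% to 46–52% (0.40 + 0.60 × 0.10; 0.40 + 0.60 × 0.20), but the 6–12 point artefact requires none in control. With 10% in both arms, both read 46% and the difference is zero.

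It can also be said that coding the cluster belongs in an analysis plan that is not shown. That would hold if the protocol were merely silent. Here two of its sections conflict on whether a control man has one HCF, and that cannot be settled after randomisation without knowledge of attendance.

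Finally, wider log searching exposes more identities in a setting where disclosure can harm. That objection stands and shapes the fix.

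**Conclusion.** The point holds as a defect of definition and procedure, and should be corrected before follow-up. The log check starts from self-report in both detailed descriptions, its scope is stated in three ways, and the abstract and Step 8 disagree on whether a control man has one HCF. Followed as written, men who report no test and about 44 non-attenders go unchecked. The mixed model also has no defined cluster for control men who do not test.

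The 44 rest on the planned 80% retention. The cluster conclusion rests on Step 8 governing control men; if the abstract governs, each man has an HCF and the repair is to say so consistently.

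Bias by arm is a possibility in a testing-promotion trial and is not demonstrated. The rejection rates above show only that unequal capture would matter if it occurred; they estimate nothing about this trial.

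**What to change.** 1. **Reconcile the abstract, Step 8 and Confidentiality and security of data.** Record one index HCF per man at randomisation, in both arms, in his own city and matching his arm. Use it as the cluster in the mixed model wherever he tests, or if he does not test.
2. **Use one log-check rule for both arms.** At six months, study nurses check the test logs of the participating HCFs for every man who signed the records release, whatever he reports and whether or not he attends the survey.
3. **Use a match key more reliable than a first name or alias**, for example phone number, and state who supplies it to the nurse.
4. **Keep self-report for tests elsewhere.** Report verification rates by arm, and present log-verified testing at participating HCFs as a sensitivity analysis. Set in advance how a non-attender is counted: an entry in the log shows a test, but no entry does not exclude a test elsewhere. Adding only the log-positive non-attenders to the main outcome would raise the rates artificially.

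Cost: protocol wording, one extra field at randomisation, and some log-search time for nurses already in the plan. The real downside is added handling of identifiers. The consent and release wording must expressly cover the search, since the present text ties confirmation to men who report a test. The existing confidentiality safeguards must be kept.

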#### Data storage and access

Paper documents (HCF surveys) will be entered into an electronic database, verified, and destroyed immediately upon verification. The link between the participant ID number and identifiable information will be limited to approved study personnel on a “need to know” basis. The file will be password protected and stored on an encrypted server in a location with no survey data. This link will be kept until study completion, at which point it will be destroyed by the site PI. Additionally, all data from the study (whether identifiable or not) will be stored on an encrypted server, in a password protected folder.

To limit possible loss of confidentiality with the audio files, all qualitative data (HCF staff and MSM; FGDs and IDIs) will be protected using the following measures: 1) audio files will be internally transcribed as soon as possible, but within no more than 14 days after the interview date and all identifying information will be removed; 2) a second staff member will listen to the transcripts to verify they have been correctly transcribed and ensure no remaining identifying information is present; and 3) audio files will be permanently destroyed.

No one outside of the MPIs, research assistant and study medical director and healthcare providers with a clinical “need to know” will have access to any identifiable data. The research assistant will need access to basic identifying data such as name, phone number for follow-up contact purposes to aid in recruitment, enrollment and data collection. If an urgent clinical issue arises (such as, a participant experiencing acute psychological distress) it may be necessary to link the participant’s contact information to subject’s identity to provide clinical follow-up. No data will be shared without the participant’s written informed consent to release medical information. It is in keeping with the principle of beneficence to ensure continuity of care by making it possible (not mandatory) for participants to share information with a medical provider.

All data will be identified only by the subject ID number, and no participant names will appear on any research materials. MSM participants will be followed longitudinally and a minimal amount of contact information (phone, email, first name or alias) will be linked to the data by use of a corresponding Participant ID. The link between the participant ID number and identifiable information will be limited to approved study personnel on a “need to know” basis. The file will be password protected and stored on an encrypted server in a location with no survey data. This link will be kept until study completion, at which point it will be destroyed. Participation in the study does not involve more than minimal risk.

